#### Intervention Design

2.3.3

The LEAD clinical trial is intended to be self-administered and delivered through a comprehensive, interactive, web-based platform designed according to recommended functionalities and user-designed principles [63]. Through three distinct modules (See Table 1), the LEAD clinical trial will facilitate the advance care planning processes of 1) defining the care recipient’s care values and preferences, 2) developing advance care planning congruence within the dyad, or a shared understanding of the care recipient’s values and preferences, through conversation(s), and 3) encouraging ongoing advance care planning conversation and sharing of documentation beyond the dyad. These processes are the foundation of Module 1: Individual, Module 2: Together, and Module 3: Documentation and Sharing.

All modules will include video tutorials introducing the goals and tasks of each module, as well as interactive resources relevant to the content of each module (e.g., review of dementia progression, explanation of life-sustaining treatment options, communication techniques for difficult conversations) [63]. In Module 1, each dyad member completes the LEAD Guide. The care recipient completes based on his/her values and preferences for their end-of-life care, and the care partner completes the LEAD Guide based on how they believe the care recipient will respond to each question. In Module 2, the dyad will video-record themselves, utilizing a built-in video-recording software, comparing their responses on the LEAD Guide as they identify areas of congruence and discordance. Following their conversation, they will complete the LEAD Guide together if revisions are needed based on their conversation. In Module 3, participants are to revise and save formal advance care planning documents and record additional conversations, creating a web-accessible archive of conversations and thoughts about advance care planning values and preferences [63]. The three modules follow a sequential pattern, each prompted one week apart, giving participants time to learn, reflect, and complete the tasks. As shown with light-gray arrows in Figure 3, the dyad may revisit any of the three modules during the 5-month study period [63].

For eventual real-world implementation, the dyad would have access to the three modules, including the document-storage/sharing functions, allowing them to revisit advance care planning as the disease progresses or conditions change. Participants will see a dashboard similar to Figure 4, which tracks completing the recommended tasks associated with each intervention module. The dashboard indicates which tasks have been or still need to be completed [63]. All participants will receive weekly auto-generated messages (text or e-mail, based on communication preference at enrollment) reminding them of each module’s tasks, resources, and tools.

#### Benefits for Participants and Researchers

2.3.4

A web-based intervention will provide several advantages for the study participants and the study team [63]. For study participants, a web-based intervention will 1) create a convenient, home-based, self-administered intervention program, 2) allow study participants the opportunity to save and electronically disseminate their completed advance care planning documents to extended family members and healthcare providers, 3) serve as a personal archive for video files of advance care planning conversations, and 4) provide easy access to the research team for comments, questions, or concerns. For the research team, a web-based intervention will afford 1) the creation of informational videos on how to engage in challenging advance care planning conversations as well as providing an exemplar discussion, 2) integration of data collection with intervention procedures by allowing participants to video-record conversations and document other real-time information about their end-of-life values and preferences, 3) the ability to auto-send information and personalized reminders to participants to increase treatment fidelity and participant adherence, 4) reduced study costs by minimizing the need for trained facilitators and by minimizing missing data and participant attrition given the ease of intervention completion in one’s own home and at one’s convenience, and 5) potential for national recruitment of research participants, given that dyads can access the LEAD clinical trial from anywhere.

### Research Design

2.4

#### Timeline

2.4.1

Our study procedures have two distinct stages, which correspond to the Stage 1A and Stage 1B activities outlined by the NIH stages of behavioral intervention development and testing [85]. In Stage 1A, we will refine the LEAD clinical trial as a web-based intervention, using a collaborative and iterative process consisting of technical development, feedback, refinement, and user testing. In Stage 1B, we will conduct a mixed-method evaluation of the web-based LEAD clinical trial to understand the process and outcomes of advance care planning in diverse community-based ADRD dyads. Together, these two stages will refine and evaluate the web-based intervention’s feasibility, usability, and initial efficacy. We will use the RE-AIM Framework [123] as a general orienting framework to guide our evaluation. RE-AIM, standing for Reach, Efficacy, Adoption, Implementation, and Maintenance, will serve to identify the essential elements that will help us create an evidence-based intervention that is effective, generalizable, and ultimately scalable to widespread use and adoption in the real world.

In Stage 1A (Years 1–2), we will collaborate with our community advisory board and the Genetic Science and Learning Center at the University of Utah in the development, prototyping, and refinement of the LEAD clinical trial as a comprehensive, interactive, and user-friendly platform for older adults and others with cognitive impairment [63, 107–109, 124, 125]. The Genetic Science and Learning Center team includes software engineers, programmers, graphic designers, media producers, and project managers who create web-based applications for healthcare interventions. Our community advisory board will provide feedback at least four times during the intervention-development process, primarily focusing on the imagery, language, and user instructions that are most relevant and easy to use for participants. The media team will produce a series of informational and instructional videos for the web-based intervention platform using a similar collaborative and iterative process used to receive feedback from the board.

In Stage 1B (Years 2–5), we will evaluate the web-based LEAD clinical trial with a sample of community-based ADRD dyads. We will use an integrated mixed-method study design to address three Specific Aims, corresponding to 1) the acceptability, usability, and feasibility of the LEAD clinical trial, 2) the initial efficacy of the LEAD clinical trial on the primary outcome (decision-making self-efficacy) and secondary outcomes (relationship quality, subjective well-being, anxiety), and 3) exploring advance care planning congruence as a mechanism of action for the LEAD clinical trial.

#### Procedures

2.4.2

Upon consent and enrollment, each dyad member will receive a username and password that will grant them access to the LEAD clinical trial web-based platform, where they will first complete a baseline assessment. The intervention modules, post-intervention, and follow-up assessments will be sequentially unlocked when the previous step is complete. The baseline survey, as well as the mid-intervention (Week 3), post-intervention (Week 8), and follow-up assessments (Weeks 14 and 20), provide both quantitative scores and open-ended narrative responses for key variables. This longitudinal study design will provide a total of five repeated measures of outcome variables; decision-making self-efficacy [126], relationship quality [127], anxiety [128], and well-being [129]. See Table 2 for details.

Participants will access the LEAD clinical trial immediately after completing the baseline survey and will have four weeks to complete the intervention tasks. Additional data will be collected directly from the LEAD clinical trial website. This data includes video recordings of advance care planning conversations (Module 2). In addition, data includes a series of usability, acceptability, and feasibility measures collected within and after the completion of each module (Modules 1, 2, 3). Lastly, Google Analytics will track end-user statistics, such as participant navigation and utilization of the LEAD clinical trial features.

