### Recruitment and Retention

2.2

We will use a convenience sample of 60 study dyads (120 persons) to evaluate the LEAD clinical trial. We are explicitly looking for persons in the preclinical or early stage of cognitive decline who have not previously engaged in advance care planning. Older adults with subjective cognitive complaints and those with mild cognitive impairment are at increased risk of progressing to dementia compared with their cognitively normal counterparts [88–93]. Persons beyond the early stage of ADRD may find challenges in the tasks required for data collection and intervention participation [94–96]. In contrast, those who have yet to engage in advance care planning can receive coaching on how to engage in comprehensive advance care planning [60, 64, 97, 98]. In order to broaden recruitment opportunities and because this is a community-based (rather than clinic-based) study, we will not administer any cognitive screening assessments or verify self-reported diagnoses.

Drawing from our prior experience [79–80], we will use three national research registries for recruitment: ResearchMatch^©^, TrialMatch^©^, and Clinical Trials^©^. ResearchMatch^©^ is a national health-research volunteer research registry supported by the U.S. National Institutes of Health as part of the Clinical Translational Science Award program. TrialMatch^©^ is a free matching service supported by the National Alzheimer’s Association that connects individuals with ADRD, care partners, and healthy volunteers to authorized clinical research studies. Clinical Trials^©^ is a National Institutes of Health registry of publicly and privately funded clinical trials. To preferentially recruit communities that have historically been less likely to adopt advance care planning (racially/ethnically diverse groups, LGBTQ individuals) [36–38], we will engage in University-affiliated and community-based recruitment strategies.

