##### Aim 1:

To describe the acceptability, usability, and feasibility of the LEAD clinical trial, we will use data from the web-based feasibility surveys conducted immediately after the completion of Modules 1, 2, and 3, as well as analytics tracked in the back-end database of the intervention.

To assess feasibility, we will use measures including the time required to identify and recruit 60 dyads, the percent of the enrollment of eligible participants (60/100, or 60%), and retention rate and data completion (85% retention at the end of the intervention; 75% retention to 14-week follow-up; 70% through 20-week follow-up).

To assess the acceptability, feasibility, and appropriateness of the LEAD clinical trial, we will use a validated scale developed by Weiner et al. [130] (Cronbach’s α = 0.85 to 0.91). Each domain includes four Likert-type questions from 1 (Completely Disagree) to 5 (Completely Agree). Our benchmark for success will be a mean of the four items ≥ to 4 on each domain. We will ask a final open-ended question, “Do you have any comments or suggestions for the LEAD clinical trial?” for intervention refinement.

The usability of the LEAD clinical trial is related to end-user behaviors using Google Analytics to describe participant navigation and utilization of the LEAD clinical trial features. These data will describe, for example, which features and resources are utilized the most by participants. These data will also track which participants created, stored, or shared advance care planning documents within the functionality of Module 3.

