For Aim 2, we will assess the initial efficacy of the primary (decision-making self-efficacy) and secondary (relationship quality, anxiety, subjective well-being) outcomes for the dyads enrolled in the study. Because individuals are distinguishable (care recipient and care partner) and nested in pairs, bivariate response models are utilized to model the dyad for changes in outcomes across the study. We will utilize time as a categorical variable to allow more flexibility in examining evolution in the primary and secondary outcomes across the five-time points of baseline, midpoint, post-intervention, and 14-week and 20-week follow-ups. This process allows for separate estimation of fixed effects of means for the care recipient and the care partner and allows random variation for the baseline intercepts. Finally, because repeated measures are correlated, and measures between individuals nested in pairs are likely to be correlated, the models will include a covariance matrix that allows for these associations. Our alternative hypothesis is that mean decision-making self-efficacy and secondary outcomes will improve in the care recipient and care partner over time. Additional exploratory covariates will include the dose (number of completed modules), relationship type (spousal/partner versus child-parent), and care recipient gender.

Qualitative descriptive analysis [41, 42] identifies and analyzes themes from open-ended narrative responses associated with these outcome measures. This method emphasizes a “data-near” approach, accepting the respondent’s statement as an accurate representation of their experience.

For Aim 3, qualitative analysis creates profiles of dyads under different categories of both practical and dyad outcomes: ADRD status (preclinical or early stage ADRD), relationship type (spouse/partner or adult child), and education level (of the care recipient). Conversation analysis coding and interpretation will incorporate and expand on themes identified earlier using qualitative descriptive analysis. Coding will also explicate and interpret individual and dyadic responses to the use of the LEAD clinical trial, specifically the process of change in advance care planning congruence. The analysis will further illuminate the relationship quality of dyads and the decision-making self-efficacy of the care partner, providing innovative triangulation of data obtained from self-reported measures and providing a deeper and richer analysis for this aim.

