#### Sample Size

2.5.3

The sample has ample statistical power for the proposed analyses. For example, Aim 1 evaluates feasibility, acceptability, and usability. With a total sample of 60 dyads, we expect reasonable descriptive parameter estimates and narrow 95% confidence intervals for all quantitatively assessed indicators. For example, 60% enrollment starting from a population of 100 dyads has an estimated 95% CI of [50.2%, 69.8%]. Similarly, if we anticipate that 85% of participants complete the surveys post-intervention, a sample size of 60 dyads at baseline has an estimate and 95% CI of 85% [76%, 94%].

Aim 2 examines the initial efficacy of the LEAD clinical trial on primary and secondary outcomes over time utilizing bivariate response models. Power and sensitivity analysis were computed in MPLUS and SAS using a bivariate model with time as a categorical variable and accounting for repeated measures and nesting of dyads. For this study, we will assume differences between 0.2 and 0.4 SD for the care recipient and care partner over time. With 42 dyads (the number of dyads expected to complete all three modules), this gives us greater than 91% power to detect these effects for dyads with complete data. Because our bivariate model analyses use intention-to-treat data from all participants regardless of missing time points, this provides a conservative power calculation for our expected sample size of 60 dyads.

Analyses for Aim 3 are composed of both qualitative and quantitative sub-aims. The proposed study is powered to address Specific Aims 1 and 2 with 60 participant dyads. Aim 3 is descriptive, focusing on mean differences in decision-making self-efficacy based on advance care planning congruence and exploring patterns of change over time based on baseline congruence.

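### Outcome surveys are chained to completion of earlier steps, so Week 8 to 20 data would go missing by adherence while the efficacy analysis is called intention-to-treat

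*Protocol article*

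**What the plan says.** All references are to the protocol article.

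- **Release rule (2.4.2, Procedures).** "The intervention modules, post-intervention, and follow-up assessments will be sequentially unlocked when the previous step is complete". Intervention steps and outcome surveys form one chain, and the trigger is completion. The Week 3 survey is not named in this sentence.
- **Schedule (2.4.2).** The baseline survey is listed "as well as the mid-intervention (Week 3), post-intervention (Week 8), and follow-up assessments (Weeks 14 and 20". Participants "will have four weeks to complete the intervention tasks". The text does not say what happens to the surveys if tasks are unfinished when that window closes.
- **Analysis claim (2.5.3, Sample Size).** "our bivariate model analyses use intention-to-treat data from all participants regardless of missing time points".
- **Expected numbers.** Section 2.2 states: "We will use a convenience sample of 60 study dyads (120 persons) to evaluate the LEAD clinical trial". Section 2.5.1, Aim 1, sets the targets "85% retention at the end of the intervention; 75% retention to 14-week follow-up; 70% through 20-week follow-up". Section 2.5.3 anticipates 85% completion of the post-intervention surveys, and bases its power statement on this: "With 42 dyads (the number of dyads expected to complete all three modules").
- **Dose (2.5.2, Analytic Plan).** "Additional exploratory covariates will include the dose (number of completed modules").

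**The concern.** This is a single-group, before-after study, so change from baseline is the whole efficacy estimate. If the platform offers the Week 8, 14 and 20 surveys only to dyads that have completed everything before them, whether an outcome is observed depends on adherence. Adherence may well be related to how confident and how well the dyad feels.

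A likelihood-based repeated-measures model handles missing visits properly only if they are missing at random given what was observed. For a dyad that stops in Module 1 or 2, that is a baseline score and perhaps a Week 3 score. The model then fills in its later course largely from dyads that finished. The result would be reported as the change in all enrolled dyads.

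Two further things are at stake. A dose effect on later outcomes cannot be learned if everyone with later outcomes has the same dose. And no later analysis can recover answers that the platform never asked for.

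**Working it through.** **1. The plan's own figures.** With 60 dyads:
- 85% at the end of the intervention: 0.85 × 60 = 51
- 75% at Week 14: 0.75 × 60 = 45
- 70% at Week 20: 0.70 × 60 = 42

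The stated interval for 85% of 60 also reproduces: 0.85 ± 1.96 × √(0.85 × 0.15 / 60) gives 76.0% to 94.0%. So 42 is exactly the Week 20 retention target, although section 2.5.3 labels it as the number finishing all three modules.

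**2. Do the figures fit the release rule?** If 42 really means module finishers and Week 8 opens only after Module 3, at most 42 dyads can be offered Week 8 or any later survey. Against 51 expected at post-intervention the shortfall is 51 − 42 = 9. Against 45 at Week 14 it is 45 − 42 = 3. On this reading 60 − 42 = 18 dyads (30%) have no outcome after Week 3. If 42 is instead Week 20 retention, the sequence 51, 45, 42 is compatible with the rule, but the label in 2.5.3 is then wrong and the expected number of finishers is not stated.

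**3. Dose.** Under the rule, a dyad with a Week 8 or later score has completed all three modules. Dose equals 3 for every such dyad, so it cannot explain differences in post-intervention outcomes.

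**4. Illustration of the bias.** Assumptions, none from the documents except the range of effects (0.2 to 0.4 SD in 2.5.3) and the 70% from 42/60:
- finishers and non-finishers do not differ at baseline;
- the correlation between visits is 0.6;
- half of the Week 8 change is present by Week 3;
- no non-finisher is measured after Week 3.

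All-dyad change = 0.70 × (finishers' change) + 0.30 × (non-finishers' change). The likelihood estimate regresses Week 8 on the earlier scores in finishers, averages the predictions over all 60 dyads, and subtracts the baseline mean (3,000 simulated trials per row).

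| Finishers | Non-finishers | All-dyad change | Estimate, baseline kept | Estimate, Week 3 also kept |
|---|---|---|---|---|
| 0.20 | 0 | 0.14 | 0.199 | 0.192 |
| 0.20 | 0.10 | 0.17 | 0.201 | 0.199 |
| 0.30 | 0 | 0.21 | 0.299 | 0.285 |
| 0.30 | 0.15 | 0.255 | 0.303 | 0.290 |
| 0.40 | 0 | 0.28 | 0.396 | 0.373 |
| 0.40 | 0.20 | 0.34 | 0.399 | 0.391 |

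Hand check of the fifth row with Week 3 kept: the Week 3 coefficient is 0.6 / (1 + 0.6) = 0.375, and non-finishers are 0.20 lower at Week 3. Their predicted Week 8 mean is 0.40 − 0.375 × 0.20 = 0.325, and the average is 0.70 × 0.40 + 0.30 × 0.325 = 0.378. This is within 0.005 of the simulated value.

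If 85% finish instead, with non-finishers at 0, the all-dyad change is 0.85 × 0.40 = 0.34 and the simulated estimate is 0.401.

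**5. How much of this is due to the unlock rule?** Suppose a fraction f of non-finishers would answer under date-based release, that they are typical of non-finishers, and that all finishers answer. With baseline kept, the estimate is then (0.28 + 0.30 × f × d) / (0.70 + 0.30 × f), where d is the non-finishers' change.
- f = 0: 0.40, so the rule changes nothing.
- f = 0.5 (42 + 9 = 51 dyads, which happens to match the 85% target): 0.28 / 0.85 = 0.33 if d = 0, or (0.28 + 0.03) / 0.85 = 0.365 if d = 0.20. The rule accounts for about 0.07 of a 0.12 SD bias, or 0.035 of a 0.06 SD bias.
- f = 1: the rule accounts for all of it.

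**The case against.** The strongest reply is that the lockout rests on one sentence in a condensed article. The sentence does not define a step or its completion. Surveys are placed at calendar weeks, and Week 8 falls after the four-week task window, so date-based release may be what was meant. Expecting 51 dyads at post-intervention alongside 42 module finishers also suggests that the authors did not intend to restrict surveys to finishers. This stands as a reason for doubt about intent. It does not remove the problem, because the article states completion as the trigger and nowhere states release by date.

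Four stronger conclusions that a reader might draw are not supported:

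- *That the efficacy analysis becomes completers-only.* All baseline data remain in the bivariate model, and Week 3 may remain too. The weakness is the missing-at-random assumption, not the analysis set.
- *That the 85% and 75% retention targets cannot be reached.* This needs the literal label on 42. Read as 70% of 60 at Week 20, the targets are coherent.
- *That retention and module completion become the same number.* Completion is only an upper bound on survey retention, because finishers can still miss Weeks 8, 14 or 20.
- *That the effect is overstated by 43%.* That is 0.40/0.28, and it needs exactly zero change in non-finishers, only baseline kept, and full follow-up under the alternative. With half the gain the ratio is 0.40/0.34, about 18%. The plan itself expects losses of 15% to 30%, and many dyads that stop the modules would not answer surveys either.

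It is also fair that dose is only an exploratory covariate and that this is a Stage 1 study of initial efficacy.

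**Conclusion.** The point holds as a conflict between a stated design rule and the stated analysis. Taken as written, section 2.4.2 withholds later outcome surveys from willing dyads that stall or miss a survey. The Week 8 to 20 estimates then lean towards finishers' change, while section 2.5.3 describes them as intention-to-treat data from everyone. The planned dose covariate has no variation among dyads with Week 8 or later data.

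The size is not known from the documents. With 70% finishing and finishers gaining 0.40 SD, the estimate would be about 0.37 to 0.40 SD against 0.28 SD for all dyads if non-finishers gain nothing. It would be about 0.39 to 0.40 SD against 0.34 SD if they gain half. These gaps are upper limits for the effect of the rule, which shrinks towards zero as fewer non-finishers would have answered anyway.

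The figure of 42 needs attention on either reading. As module finishers it does not fit 51 and 45 dyads under the rule; as Week 20 retention it is mislabelled.

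**What to change.** - In 2.4.2, apply sequential unlocking to the modules only. Release the Week 3, 8, 14 and 20 surveys to each dyad member by date from that dyad's baseline, whatever the module progress and whichever earlier surveys were missed.
- In Aim 1, report survey retention and module completion as separate measures.
- In 2.5.3, state whether 42 is the expected number of module finishers or the Week 20 retention figure, and correct the label if needed.
- If completion-based release is deliberate, say so, stop describing the Week 8 to 20 estimates as intention-to-treat, and add a sensitivity analysis that allows data missing not at random.

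The cost is a small change to the platform's release logic and a few sentences of text. It is best made before the first dyad enrols; the article anticipated enrolment from the first quarter of 2024 and does not give the build status. The downside for the sponsor is that the mean change may look smaller once some non-finishers answer. Date-based release will not remove all loss to follow-up, only the part that the platform itself creates.
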